**2.3.4.2. Functional outcomes**

**Snoring**

Snoring will be assessed based on the question “Do you snore” with the following responses: “never,” “rarely,” “sometimes,” “often,” and “almost always.” Based on these responses, 3 groups will be created: [1] “Never” or “Rarely,” [2] “Sometimes,” and [3] “Often or Almost Always”.

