#### 2.3.2. Health status.

We will collect data on lifestyle habits related to alcohol and tobacco consumption, dietary habits, internet use, analgesics/anxiolytics/hypnotics consumption, physical activity, sleep-wake habits, and sleep duration. We will also collect data on prevalent morbidities such as nasal allergy, asthma, chronic obstructive pulmonary disease **(COPD)**, cardiovascular and metabolic diseases as well as depression.

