#### 2.3.4. Outcome measures.

Our prespecified primary outcome is CPAP adherence measured in h/night at 1, 3, and 6 months after starting CPAP therapy. Our secondary outcome is functional status at the 6-month follow-up, which includes snoring, nasal obstruction symptoms, subjective quality of life, fatigue, emotional status, cognitive function, insomnia and EDS.

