### 2.6. Protocol study

After a nocturnal polygraph recording showed severe OSAHS, the patient will be seen by a sleep doctor the following day. The doctor will explain the diagnosis and the need for CPAP therapy. The patient will then complete an informed consent form to participate in the study and be randomly assigned to either the usual care (n = 30) or the TPE group (n = 30). Additionally, the patient will fill out a questionnaire covering sociodemographic data, health status, NOSE questionnaire, WHO-5 questionnaire, HAD questionnaire, FSS questionnaire, MoCA questionnaire, ESS questionnaire and ISI questionnaire. Following this, the patient will be scheduled to start CPAP therapy within 1–2 weeks after the nocturnal polygraph recording.

Following the TPE session, patients in the TPE group will be provided with CPAP devices to take home. They will be advised to call the sleep nurses if they experience any side effects. The phone line will be available on weekdays from 9:00 am to 4:00 pm, and patients can leave a message at other times. An assigned nurse will contact patients on the second and fifteenth days to identify and resolve any CPAP-related issues. The SDC CPAP Questionnaire will be administered by the nurse for each patient in this group on day 2 following CPAP titration.

Patients in the usual care group will be advised to consult the CPAP technician for any questions or concerns.

Both groups of patients will be scheduled for follow-up appointments with a CPAP technician and a sleep physician on day 15 (only if the CPAP perception score is poor) and at 1, 3, and 6 months after starting CPAP therapy. During each visit, we will assess adherence to and tolerance of CPAP by asking questions about side effects and reviewing CPAP SD Card data. Any CPAP-related issues reported by the patients will be addressed accordingly. At the 6-month follow-up, all patients will be asked to complete the functional outcomes questionnaires once again (Figs 1 and 2). Sleep physicians involved in the routine clinical follow-up of the patients will be blinded to each patient’s treatment group.

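### The snoring item sets neither a recall window nor a CPAP condition, so its month-6 comparison is ambiguous, and section 2.6 is inconsistent on whether it is asked at baseline

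*Protocol article*

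**What the plan says.** Section 2.3.4 of the protocol article defines the secondary outcome as "functional status at the 6-month follow-up, which includes snoring" and seven further components.

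The Snoring paragraph of section 2.3.4.2 sets the measure: "Snoring will be assessed based on the question “Do you snore” with the following responses", with five answers running from never to almost always. It continues: "Based on these responses, 3 groups will be created". It states no recall window and does not mention CPAP.

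Section 2.6 lists what the patient completes at enrolment, including "health status, NOSE questionnaire, WHO-5 questionnaire, HAD questionnaire, FSS questionnaire, MoCA questionnaire, ESS questionnaire and ISI questionnaire". Snoring is not named. Section 2.3.2, which describes health status, comes closest with "physical activity, sleep-wake habits, and sleep duration" and does not name snoring either. Later in section 2.6 the text reads: "At the 6-month follow-up, all patients will be asked to complete the functional outcomes questionnaires once again".

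Section 2.7 plans Pearson chi-square or Fisher's exact test for categorical variables. It reserves Mann-Whitney for continuous variables that are not normally distributed.

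**The concern.** All enrolled patients receive a CPAP device, so at month 6 a present-tense question about snoring can refer to at least three things: sleep with the mask on, the hours or nights without it, or a general tendency. A consistent full-night user or a patient who has stopped CPAP has little difficulty. A partial user does, and partial use is what this adherence trial studies.

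If patients in both arms mix these readings in the same way, a real difference in treated snoring is diluted. If the arms mix them differently, the observed difference partly reflects how the question was understood, and randomisation does not remove that. Different mixing is conceivable because the trial expects CPAP use to differ by arm, and because only the education arm sees a video contrasting life before and after CPAP (section 2.4.3).

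The baseline matters separately. Staff who follow the itemised list in section 2.6 would not ask the question at enrolment, and an untreated answer cannot be collected once CPAP has started.

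**Working it through.** The document gives no rate, effect size or power for snoring, so there is no figure to reproduce. The check is mainly textual.

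**Recall window, by component (section 2.3.4.2)**

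| Component | Instrument | Window stated | In the section 2.6 baseline list |
|---|---|---|---|
| Snoring | single question | none | no |
| Nasal obstruction | NOSE | past month | yes |
| Quality of life | WHO-5 | two weeks | yes |
| Fatigue | FSS | past week | yes |
| Emotional status | HADS | past week | yes |
| Cognitive function | MoCA | not applicable (performance test) | yes |
| Insomnia | ISI | none | yes |
| Daytime sleepiness | ESS | 3 months | yes |

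Snoring is the only one of the eight without an entry in the baseline list, and the only one not tied to a validated Arabic version of an instrument.

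**Baseline.** The list omits snoring. The later sentence in section 2.6 describes month 6 as a repeat of the functional questionnaires, and snoring is the first item under the Functional outcomes heading. The two statements do not agree. Neither settles the matter, and the schedule figures are not shown.

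**Objective substitute.** Section 2.3.3 records snoring by microphone at the diagnostic study, but the indices it lists for collection are OAHI, ODI and T90%. The device data in section 2.3.4.1 are residual AHI, usage time and leak. No objective snoring measure is listed at either time point.

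**Direction of the effect (illustration; every input is assumed).** Let *p* be the proportion snoring often or almost always with CPAP on, *u* the proportion without it, and *m* the share of an arm answering for the untreated state. Then

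observed proportion = (1 − *m*) × *p* + *m* × *u*.

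Take *p* = 10% (education) and 30% (usual care), a 20-point difference, with *u* = 80% in both arms.

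- Equal mixing, *m* = 0.5 in both: 0.5 × 10 + 0.5 × 80 = 45%, and 0.5 × 30 + 0.5 × 80 = 55%. The gap is 10 points. With equal *m* and *u*, the gap is always (1 − *m*) times the on-CPAP gap.
- *m* = 0.2 (education) and 0.6 (usual care): 0.8 × 10 + 0.2 × 80 = 24%, and 0.4 × 30 + 0.6 × 80 = 60%. The gap is 36 points.
- The reverse, *m* = 0.6 and 0.2: 0.4 × 10 + 0.6 × 80 = 52%, and 0.8 × 30 + 0.2 × 80 = 40%. The gap is 12 points in the other direction.

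These scenarios show that the ambiguity can shrink, inflate or reverse a contrast. They are neither an estimate nor bounds for this trial.

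**The case against.** The strongest objections, and what remains of each:

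- **The article may condense the form.** The question is an English rendering for Arabic-speaking patients, and lead-in text or a time frame may sit in the case report form. The description of the ISI also omits a window, so silence in print does not prove absence. This tempers the point. However, the article prints the question, all five answers and the grouping rule, so it presents the working definition, and that definition leaves the window and the CPAP condition open.
- **A baseline may well be collected.** This stands. A reader might infer from the itemised list that snoring is not measured at enrolment. The month-6 sentence points the other way, so this is an inconsistency and not a proven omission.
- **The trial is randomised.** This stands. A reader might conclude that the month-6 answer cannot show benefit at all. That does not follow. Section 2.7 describes comparisons between groups and no analysis of change, so a missing baseline would cost precision and within-patient change but would not invalidate the contrast. The unclear wording makes interpretation uncertain, not impossible.
- **Reading that differs by arm is undemonstrated.** This also stands. Usual-care patients too receive an oral explanation of the disease and of CPAP, and nothing shows that the arms understand the question differently.
- **Merging answers in advance is legitimate.** It is, but an unordered test on three groups discards the order of the answers, and the plan gives no reason for that.

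**Conclusion.** The point holds as a problem of definition. As printed, the snoring item has no recall window and no CPAP condition, so a month-6 difference between arms cannot be read unambiguously. Dilution requires only that some partial users answer for the untreated state. Distortion further requires the arms to differ in how they read the question, which is plausible but not shown. The document supports no figure for either effect. Section 2.6 also needs to be reconciled with itself on whether the item is asked at enrolment.

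Severity is minor to moderate. Snoring is one of eight components of the secondary outcome, and the primary outcome, CPAP hours per night read from the device card, is unaffected. The verdict assumes that the printed question is the one patients are given. If the form already states a window and a CPAP condition, reporting them would settle the main point.

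**What to change.** 1. Give the item a fixed window and condition. For example, at both visits: *Over the past 4 weeks, how often did you snore, or were told you snored, at any time during the night?* At month 6 only, add: *counting all sleep, with or without CPAP.* The addition is not needed at enrolment because previous CPAP users are excluded (section 2.2). Asking about any time in the night covers the patient who removes the mask partway through. The item then measures snoring over all sleep, so better adherence can show in the answer.
2. Name the item in the baseline list of section 2.6, to be asked before CPAP starts, so that the list agrees with the month-6 sentence.
3. Compare the arms on the five ordered answers with a rank-based or ordinal test, and keep the three groups for display. This extends section 2.7, which plans Mann-Whitney only for non-normal continuous variables, so the change should be written in.

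The cost is one reworded question asked at two visits and one added sentence in the analysis section. The downside is slightly less comparability with surveys that use the unmodified item.

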### 2.7. Statistical analysis

The data analysis will be conducted using SPSS Statistics for Windows, Version 23.0 (IBM SPSS Statistics for Windows, Version 23.0. Armonk, NY: IBM). We will use the Kolmogorov-Smirnov test to assess the normal distribution of data. Continuous variables with a normal distribution will be expressed as mean and standard deviation **(SD)**, while non-normally distributed variables will be represented as median and interquartile range **(IQR)**. For comparing means of 2 and 3 or more categories of normally distributed continuous variables, independent Samples t-test and ANOVA test will be used, respectively. Medians of non-normally distributed continuous variables will be compared using non-parametric tests (Mann-Whitney U test and Kruskal-Wallis). Categorical variables will be presented as counts and frequencies. The frequencies of categorical variables will be compared using Pearson χ2 or Fisher’s exact test, as appropriate. A significant level of p < 0.05 will be considered.

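### Snoring at month 6 is collapsed from five ordered answers to three groups and, under the general rule for categorical variables, compared by a test that ignores order; this loses power under a one-directional shift (minor).

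*Protocol article*

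**What the plan says.** Section 2.3.4 makes snoring part of the secondary outcome: "Our secondary outcome is functional status at the 6-month follow-up, which includes snoring, nasal obstruction symptoms". The list there has eight components: snoring, nasal obstruction, quality of life, fatigue, emotional status, cognitive function, insomnia and daytime sleepiness.

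Section 2.3.4.2 defines the item: "Snoring will be assessed based on the question “Do you snore” with the following responses", followed by five answers running from never to almost always. It then fixes a grouping: "Based on these responses, 3 groups will be created: [1] “Never” or “Rarely,” [2] “Sometimes,” and [3] “Often or Almost Always".

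Section 2.7 has two routes for comparing groups. For categories: "The frequencies of categorical variables will be compared using Pearson χ2 or Fisher’s exact test, as appropriate". For measurements that are not normal: "Medians of non-normally distributed continuous variables will be compared using non-parametric tests (Mann-Whitney U test and Kruskal-Wallis". No trend or ordinal method is named. The significance level is given as "A significant level of p < 0.05 will be considered". Section 2.6 sets the arm sizes at 30 and 30.

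**The concern.** The trial's hypothesis, at the end of the Background, has a direction: education plus support should improve treatment outcomes. For snoring, that means answers moving towards the low end of the scale. Two features of the plan work against detecting such a movement.

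- **Collapsing.** Moves from rarely to never, or from almost always to often, stay inside one group and do not count.
- **Ignoring order.** A chi-square test on three groups has 2 degrees of freedom and gives the same p-value if the group labels are permuted. Part of its power goes to patterns that the hypothesis does not predict.

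The protocol gives no reason for the grouping. In a trial of 60 patients, which its own limitations section calls small, a snoring benefit could be missed that the same answers would show under an ordinal analysis. The test also yields no effect estimate for snoring.

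**Working it through.** The protocol states no power or effect size for snoring, so there is no figure of its own to reproduce. The check is a simulation.

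**Inputs from the protocol.** Five ordered levels; grouping 1+2, 3, 4+5; Pearson chi-square or Fisher; 30 per arm; significance level 0.05.

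**Assumed.** Two-sided testing (sidedness is not stated), no dropout, the usual-care distribution and the size of the effect.

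**Generating the TPE arm.** If C_k is the cumulative usual-care proportion up to level k, the TPE proportion is OR·o_k / (1 + OR·o_k), with o_k = C_k / (1 − C_k).

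Example: usual care 35/25/20/12/8% (never to almost always), OR 3.
- Cumulative: 0.35, 0.60, 0.80, 0.92. Odds: 0.538, 1.5, 4, 11.5.
- Multiplied by 3: 1.615, 4.5, 12, 34.5. TPE cumulative: 0.618, 0.818, 0.923, 0.972.
- TPE distribution: 61.8/20.1/10.5/4.9/2.8%.
- In three groups: 60/20/20% against 81.8/10.5/7.7%. *Never* alone differs by 61.8 − 35 = 26.8 points; the merged lowest group differs by 81.8 − 60 = 21.8 points.

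**Tests.**
- Planned: chi-square = Σ(O − E)²/E on three groups, replaced by the exact Fisher-Freeman-Halton test if any expected count is below 5.
- Alternative: Mann-Whitney with tie-corrected variance n1·n2/12 × [(N + 1) − Σ(t³ − t)/(N(N − 1))], on three groups and on five levels.

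**Power, 6000 simulated trials per scenario** (planned test / Mann-Whitney on 3 groups / Mann-Whitney on 5 levels, %):

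| Usual-care distribution (%) | OR 2 | OR 3 | OR 5 |
|---|---|---|---|
| Flat, 20 each | 21.1 / 28.4 / 31.6 | 45.8 / 57.4 / 63.2 | 77.8 / 86.3 / 91.5 |
| Middle, 10/20/30/25/15 | 23.1 / 31.1 / 31.6 | 49.8 / 61.3 / 64.6 | 81.6 / 89.0 / 91.8 |
| Snoring-heavy, 5/10/20/30/35 | 20.7 / 27.9 / 31.9 | 49.0 / 59.6 / 65.2 | 83.3 / 90.3 / 92.5 |
| Low snoring, 35/25/20/12/8 | 16.9 / 23.9 / 30.4 | 35.6 / 47.7 / 61.0 | 60.2 / 74.0 / 89.3 |
| U-shaped, 30/15/10/15/30 | 21.2 / 26.7 / 29.8 | 46.4 / 56.2 / 63.2 | 77.1 / 84.5 / 90.6 |

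**Reading the results for OR 2 to 5** (2.5 and 4 were also run):
- Total loss: smallest 31.6 − 23.1 = 8.5 points (middle, OR 2); largest 79.0 − 48.9 = 30.1 points (low snoring, OR 4).
- Ignoring order alone, both tests on three groups: 26.7 − 21.2 = 5.5 points (U-shaped, OR 2) to 63.2 − 48.9 = 14.3 points (low snoring, OR 4).
- Collapsing, Mann-Whitney on five levels against three: 31.6 − 31.1 = 0.5 points (middle, OR 2) to 79.0 − 63.2 = 15.8 points (low snoring, OR 4).
- In a sixth, extreme case with 60% answering *never*, the total loss is 15 to 47 points, of which up to 18 points come from ignoring order.

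**Smaller effects.** At OR 1.5, one run of 4000 trials per scenario gave 9.2–11.0% for the planned test against 12.3–14.3%, a gain of 2.4 to 4.0 points; another gave about 3 to 5. The standard error of one such power is about √(0.12 × 0.88 / 4000) = 0.5 points. At OR 1.25 the gain is 0.2 to 1.4 points.

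**Other effect shapes.**
- Each arm a mixture of CPAP users and non-users, with TPE raising the share of users by 25 to 30 points: total loss about 3 to 9 points. Collapsing cost nothing there; ignoring order still cost 6 to 10.
- A shift into *sometimes*: planned test 55.6%, five-level Mann-Whitney 25.6%.
- The middle group emptying to both sides: 70.9% against 5.6%.

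**No effect.** The planned test rejects in 3.6% to 5.3% of trials and the five-level Mann-Whitney in about 5%.

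**The case against.** The strongest reply is that no sentence says snoring will be tested by chi-square. One passage defines groups, another gives a general rule, and a condensed article may leave item-level tests to a fuller plan. Nor does the article say that the five-level answers will be discarded. That is fair: the test is an inference. It is still the only reading that section 2.7 offers, because rank tests are tied to continuous variables there.

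A reader might infer that the plan simply costs 9 to 30 points of power. The documents do not support that. They give no snoring distribution or effect size, and proportional odds is a setting that favours a rank test. Both arms receive CPAP and differ in education and support, so odds ratios of 3 to 5 for snoring are not clearly the relevant range. At modest effects both tests are weak and little is gained by switching. The reversals for non-monotone effects are real, though such patterns are not what the Background hypothesises.

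A reader might also infer that the planned test is invalid, or that the arms would differ mainly between *never* and *rarely*. The first is wrong, since the rejection rate under no effect is about 5% or lower. The second has no basis in the documents. The test itself carries no direction, but section 2.7 also presents counts and frequencies, so the direction would be visible by arm.

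Last, snoring is a single self-reported item among eight secondary components. That limits the weight of the point without removing it.

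**Conclusion.** The point holds as a minor, conditional one. The protocol fixes the collapse to three groups and, read with its general rule, an unordered test for an outcome whose expected change has a direction. Given 30 per arm, no dropout, two-sided 5% testing and a proportional-odds shift from the five non-extreme distributions, the loss is roughly 8 to 30 points at odds ratios of 2 to 5 and about 3 to 5 points at 1.5.

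The sturdier part is ignoring order, at about 6 to 15 points for odds ratios of 2 or more. The extra loss from collapsing ranges from almost nothing to about 16 points in the same scenarios and depends strongly on the distribution. The loss shrinks under the user/non-user mixture and reverses for non-monotone effects. False-positive control and the primary outcome, hours of CPAP use per night, are not affected.

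**What to change.** Before analysis, state in section 2.7 and in the snoring definition that snoring at month 6 is compared between arms on its five ordered answers by the Mann-Whitney U test, and that the three groups serve descriptive display only. Section 2.7 already names this test but ties it to non-normal continuous variables, so its scope must be extended to ordinal items. A proportional-odds model is an equally good choice and adds a common odds ratio with 95% CI.

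The cost is about one sentence in each place, with no new data, visits or patients. The proportional-odds option brings its own assumption and needs a line of explanation for readers. Either option gives up power against non-monotone patterns. The change should be made before the snoring results are seen; afterwards it would be a post hoc choice.

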**Nasal obstruction**

Chronic nasal obstruction is a common symptom among patients with OSAHS and is a known risk factor for OSAHS as well as CPAP intolerance and discontinuation. We will use a validated Arabic version of the Nasal Obstruction Symptom Evaluation **(NOSE)** scale to assess the impact of nasal obstruction on patients’ quality of life [8]. This scale is a reliable and valid self-report questionnaire comprising 5 items related to nasal obstruction symptoms experienced over the past month. Each item is scored on a 5-point Likert scale, where 0 indicates “not a problem” and 3 indicates a severe problem. The sum of the 5-item-answers is multiplied by 5, which provides a total score ranging from 0 to 100 with higher scores indicating worse symptoms. NOSE scores of [5–25], [26–50], and [50–100] represent mild, moderate, and severe nasal obstruction-related symptoms, respectively.

**Subjective quality of life**

We will use a validated Arabic version of the World Health Organization- Five Well-Being Index **(WHO-5)** to evaluate the quality of life [9]. The WHO-5 is a concise self-assessment questionnaire designed to gauge subjective well-being over the previous two weeks. It comprises five straightforward, positively phrased items that evaluate positive mood (good spirits, relaxation), vitality (being active and waking up fresh and rested), and general interest (being interested in things). Each item is graded on a 6-point Likert scale, ranging from 0 (at no time) to 5 (all the time). The total raw score is calculated by summing the scores of the 5 individual items and ranges from 0 to 5. The final score is obtained by multiplying the total raw score by 4, resulting in a total score ranging from 0 to 100, with higher scores indicating better well-being. A final score of 50 or lower suggests poor well-being.

**Fatigue**

We will use an Arabic-validated version of the fatigue severity scale **(FSS)** to measure fatigue in our participants [10]. The FSS is a self-report questionnaire with 9 items that assess the severity, impact, and frequency of fatigue on different aspects of daily life over the past week. Each item is rated on a scale from 1 to 7, where 1 indicates strong disagreement with the statement and 7 indicates strong agreement with the statement. This results in a total score ranging from 9 to 63. A total score of 36 or higher suggests moderate to severe fatigue.

